### Data and statistical analysis

#### Data management

Data are recorded and managed through a dedicated web-based software (Cleanweb Telemedicine) with secured and restricted access. Access to the system is controlled for each investigator by an individual login/password and using a secured https connection. Data are stored on a centralised server. Participants also have paper files which are anonymised and only contain the participant’s unique identification code. These are stored in a dedicated storage unit in each centre. Access to the complete final trial dataset will be restricted to the Clinical Research Unit statistician who will analyse the study data for the purpose of report and publication. Subsets of the final dataset may be shared with investigators if needed for discussion or additional analyses. Should the need arise, advice from the steering Committee will be sought and provided to the sponsor APHP who will retain ownership of the data as well as the final decision on authorising further access to data.

### Monitoring

Clinical research assistants from the sponsors research unit regularly visit all centres for on-site monitoring to ensure protocol compliance and monitor data quality according to the data management unit guidelines and clarification forms. Data entered into Cleanweb should be complete and consistent with source documents. Eligibility criteria and consent forms are checked as well as outcome measures and adverse events. No interim analyses are planned.

### Statistical analysis

The statistical analysis will be performed once the planned number of patients will have completed the study, according to the intention-to-treat principle. Each participant is analysed according to the group in which he/she was randomised. For the primary outcome (*MGQOL-15-F* at three or six months*)*, missing values will be handled through multiple imputation by chained equations. No multiple imputation will be carried out for secondary outcomes. The main analysis of the primary and secondary outcome measures will not be adjusted. Adjusted analyses on the centre will be performed but considered as secondary analyses. As there are only two centres, the centre will be modelled as a fixed effect. Two-sided tests will be used with a 5% significance level.

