### Sample size calculation

We estimated that 42 patients (21 in each arm with 1:1 randomisation) would be necessary to show a difference in changes in the *MGQOL-15-F* of 8 points between both arms with 80% power and a two-sided type I error rate of 5%, assuming the standard deviation of changes in the *MQGOL-15-F* is 9 points based on Burns et al. [28]. A difference in 8 points is considered to be a clinically meaningful change for this population. No increase in sample size for potential drop-outs was considered in the calculation.

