#### Patient description and follow-up

A descriptive analysis of inclusions and follow-up will be performed (graph of inclusions and theoretical and actual visits). All patients will be included in the analysis unless their consent is retracted and they are opposed to their data being analysed. Any drop-outs or patients having stopped the intervention early will be included in the analysis. A patient is considered a drop-out when he/she revokes his/her consent to participate in the study and thus all participation in the study will cease.

Epidemiological and clinical characteristics of patients at baseline will be described by group without statistical tests. Any violation to the protocol and reasons for drop out will be described.

The primary outcome measure, the changes in *MGQOL-15-F*, will be analysed via a Student’s test and adjustment on the centre will use ANOVA. If the distribution of the changes in the *MGQOL-15-F* between the two groups is very asymmetrical, then a non-parametric approach based on the ranks will be used for statistical testing.

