#### Secondary outcome measure analysis

For binary outcome measures a non-adjusted analysis will be carried out using Fisher’s exact tests. The analysis will then be adjusted according to the centre via a logistic regression model. The quantifiable outcome measures will be analysed using a Student’s test for the non-adjusted analysis and an ANOVA model for the analysis adjusted for the centre. A transformation (for example a logarithm) will eventually be envisaged if the distribution of variables is not compatible with the normal distribution assumption. If the envisaged transformations do not enable a symmetrical distribution, a non-parametric analysis will be used (Wilcoxon test and ANOVA on ranks).

The analysis will be performed using the R software (version 3.4.3 or later; The R foundation for statistical computing, Vienna, Austria).

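### Patients without a six-month value fall out of the secondary change-score tests, although the protocol says drop-outs are included in the analysis

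*Protocol article*

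**What the plan says.** All statements are in the protocol article.

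- **Statistical analysis** sets intention to treat for the whole analysis and plans chained-equation multiple imputation for the primary outcome, MGQOL-15-F. For the rest: "No multiple imputation will be carried out for secondary outcomes".
- **Patient description and follow-up** states: "Any drop-outs or patients having stopped the intervention early will be included in the analysis". The only exception it gives is a patient who withdraws consent and objects to use of the data. It defines a drop-out as someone who revokes consent, after which all participation ends.
- **Secondary outcome measure analysis** compares quantitative outcomes by a Student's test, then by "an ANOVA model for the analysis adjusted for the centre". Rank versions are the fallback. No baseline term and no other way of handling missing values is named.
- The outcome sections define most quantitative secondary endpoints as the M3 to M6 change: Myasthenic Muscle Score, MG-ADL, FVC, MIP, MEP, limb strength, grip strength, six-minute walk distance and questionnaire totals.
- **Sample size calculation** adds: "No increase in sample size for potential drop-outs was considered in the calculation".

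**The concern.** These statements cannot all be carried out. A drop-out between M3 and M6 has, by the article's own definition, no M6 value and so no change score. Without imputation that patient cannot enter a Student's test, an ANOVA on change or a rank test, yet the article says drop-outs will be included. The same holds for a patient who stays in the trial but misses the M6 visit.

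This is not a detail left open for a later analysis plan. The article takes a decision on imputation and names tests that need complete pairs.

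The physical-fitness and depression aims rest on these secondary outcomes. Strength and endurance are measured in one laboratory, so a missed M6 visit loses all of them at once. Randomisation follows the M3 visit, so every loss between M3 and M6 comes after allocation. It may differ by arm, because only one arm has the exercise programme. With 21 patients per arm, each loss is about 5% of an arm (1/21 = 4.8%).

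**Working it through.** **1. The plan's own figure.** Inputs from Sample size calculation: difference 8 points, SD of change 9, power 80%, two-sided 5%, 1:1. The exact two-sample t-test at effect 8/9 = 0.89 needs 20.87, so 21 per arm and 42 in total. Power at 21 per arm is 80.3%. The article's figure reproduces: "We estimated that 42 patients (21 in each arm with 1:1 randomisation) would be necessary".

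**2. Who is affected.**

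- Loss before M3: not relevant, because randomisation comes after M3.
- Stops exercising, attends M6: has a change score and is analysed as randomised.
- Drops out after M6: has a change score.
- Revokes consent between M3 and M6, or misses M6: no change score, excluded.

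**3. Power.** No effect size or missing rate is given for any secondary outcome. For scale only, take the primary design's standardised effect of 0.89 and assume equal loss in both arms:

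| Loss per arm (assumed) | Complete-case power |
|---|---|
| 0% | 80.3% |
| 5% | 78.1% |
| 10% | 75.8% |
| 15% | 73.2% |
| 20% | 70.4% |

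**4. Bias when loss depends on M3.** Assume no true effect, equal SDs at M3 and M6, correlation ρ, and loss in one arm only: 60% of the top M3 quartile, which is 0.6 × 25% = 15% of the arm.

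- The mean of the top quartile is 1.271 SD of M3. Among those observed, the M3 mean is −(0.15 × 1.271)/0.85 = −0.224 SD.
- The expected change given M3 is −(1 − ρ) × M3, so the observed mean change is (1 − ρ) × 0.224 SD of M3.
- The SD of change is √(2(1 − ρ)) SD of M3. Dividing gives a shift of 0.224 × √((1 − ρ)/2) SD of change.

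| ρ (assumed) | Shift, SD of change | Shift if SD of change were 9 |
|---|---|---|
| 0.5 | 0.112 | 1.01 |
| 0.6 | 0.100 | 0.90 |
| 0.7 | 0.087 | 0.78 |

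A simulation of 400,000 draws gave 1.00, 0.86 and 0.79, with error up to about 0.05. Under an alternative pattern, losing the 10% or 20% with the highest M3 values from one arm gives 0.10 or 0.18 SD at ρ = 0.5 and 0.08 or 0.14 SD at ρ = 0.7.

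**5. Against sampling error.** 15% of 21 is about 3 patients. With 18 and 21 analysed, the standard error of the difference is √(1/18 + 1/21) = 0.321 SD. The shift is therefore 0.087/0.321 = 0.27 to 0.112/0.321 = 0.35 standard errors.

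**6. Loss that depends on the change itself.** If a fraction d of an arm is lost and its mean change is g SD worse than the rest, the observed arm mean is too favourable by d × g. With g = 1, that is 0.05, 0.10 and 0.20 SD at 5%, 10% and 20% loss.

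**The case against.** The strongest reply is that this is a declared choice. The primary outcome is protected by imputation, and the next sentence says that the others are not imputed. Available-case analysis of secondary outcomes is common in a trial of 42. Only multiple imputation is ruled out, so an analysis plan could still name another method. On this view, the sentence about drop-outs merely describes the analysis population and needs one clarifying clause.

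Part of this stands. The choice is open and the primary analysis is not affected. But the sentence on drop-outs carries no restriction, and the tests named cannot honour it.

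Four stronger readings are tempting, and the article does not support them:

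- **That early stoppers are lost.** They are listed separately from drop-outs, and those who attend M6 keep a change score.
- **That the bias is large or favours exercise.** The SD of 9 belongs to the imputed primary outcome, and loss in one arm only is an assumption. If the most affected patients at M3 leave the exercise arm, the remaining mean change moves in the unfavourable direction, against exercise. Other patterns, such as step 6 in the exercise arm, run the other way.
- **That the tolerance conclusions fail.** These rest largely on training-session data and monthly safety assessments.
- **That any mixed model using the other visits cures it.** A model with only M6 and M9 as outcomes and M3 as covariate still has no row for a patient who left before M6. Also, anxiety and depression have no M0 value, and self-esteem and the MINI are assessed only at three and nine months.

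**Conclusion.** The point holds in this limited form. The promise to include drop-outs conflicts with unimputed tests on M3 to M6 change, and patients without an M6 value are excluded from those tests. The result is some loss of power and a possible modest bias, about 0.1 SD of change or roughly 0.3 standard errors in the illustration. That figure rests on an assumed 15% one-arm loss depending on M3 and an assumed correlation of 0.5 to 0.7. If loss is completely at random there is no bias, only lost power. The article gives no missing rate, SD or correlation for these outcomes, so neither the size nor the direction can be fixed in advance. The point is worth correcting because the better methods use data already scheduled and a technique already planned.

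**What to change.** For continuous secondary outcomes measured at both M3 and M6, choose one of these in advance:

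1. A likelihood-based repeated-measures model with M3, M6 and M9 all as outcomes, a common M3 mean across arms, arm-by-visit terms afterwards, and centre. Patients with only an M3 value are then retained.
2. Extend the planned chained-equation imputation to these outcomes and analyse M6 adjusted for M3.

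In either case report the M6 contrast, and keep the unadjusted complete-case test as a sensitivity analysis. Reword the sentence in Patient description and follow-up so that it says how drop-outs enter each analysis and which analyses use available cases only.

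The cost is a little more programming in R, with no new data. Both options assume data missing at random. They remove the bias in step 4 of the working, but not bias from loss that depends on the unseen M6 value, as in step 6.

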#### QOL and psychological state

At three, six and nine months anxiety is evaluated via the State Trait Anxiety Inventory (STAI) and depression is evaluated via the modified Beck Depression Inventory (BDI-13). Psychiatric disorders are evaluated by the Mini-International Neuropsychiatric Interview (MINI, French Version 5.0.0) and self-esteem via the Self-Esteem Inventory scale (SEI) at both three and nine months. Global QOL is measured via the World Health Organisation QOL-BREF scale and specific QOL via the MGQOL-15-F at zero, three, six and nine months. Semi-structured interviews are conducted at zero, three, six and nine months. We ask patients to draw themselves at zero, six and nine months. Evaluations are carried out during a face-to-face meeting with a clinical psychologist which lasts approximately 90 min. The mean change in the total score for each questionnaire will be compared between groups at M3 and M6 as secondary outcomes.

The STAI evaluates anxiety via a self-administered questionnaire consisting of two 20-item sub-scales: the STAI A evaluates the actual level of anxiety at the moment of the assessment (state anxiety); and the STAI B investigates more general and long-standing anxiety (trait anxiety) [45]. Scores are in the range of 20–80 for each questionnaire with higher scores indicating greater anxiety. The French version was validated by Bruchon-Schweitzer and Paulhan [46].

The SEI evaluates the judgment that an individual holds about themselves regardless of the circumstances. The self-administered questionnaire, adapted into French (ECPA, 1984), consists of 58 items with sentences describing feelings, opinions or individual reactions with either a ‘like me’ or ‘unlike me’ response [47]. It investigates self-esteem in four domains: personal (26 items); social (eight items); family (eight items); professional (eight items); and contains a lie scale (eight items). A higher score indicates greater self-esteem.

Depression is evaluated via the self-administered BDI-13 (short version), consisting of 13 items validated in French by Collet and Cottraux [48]. Each item has four response choices (0–3) and provides a global score (0–39) corresponding to depression severity (0–4 = no depression, 4–7 = mild, 8–15 = moderate, ≥ 16 = severe depression).

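### The unadjusted t-test on the M3–M6 change in MGQOL-15-F is valid but gives up precision that ANCOVA on the M3 score would recover from data already scheduled

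*Protocol article*

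**What the plan says.** Under Primary outcome measure, the protocol article defines the outcome as the change in total MGQOL-15-F (range 0–60, higher is worse) from three to six months. Under Patient description and follow-up, this change is to be compared by a Student's "test and adjustment on the centre will use ANOVA", with a rank-based test if the distribution is very asymmetrical. Under Statistical analysis the choice is explicit: "The main analysis of the primary and secondary outcome measures will not be adjusted". That section allows adjustment for centre only, as a secondary analysis.

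The section on QOL and psychological state schedules "specific QOL via the MGQOL-15-F at zero, three, six and nine months". The legend of Fig. 2 places randomisation after the M3 visit, so the M0 and M3 scores both precede allocation. Randomisation is stratified by centre.

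Under Sample size calculation, 21 patients per arm are planned for a difference of 8 points at 80% power and two-sided 5%, "assuming the standard deviation of changes in the *MQGOL-15-F* is 9 points". It adds: "No increase in sample size for potential drop-outs was considered in the calculation".

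**The concern.** A change score subtracts the M3 value and so fixes its coefficient at 1. ANCOVA estimates that coefficient. When M3 and M6 have similar variances, the best coefficient is the correlation rho, which is below 1. Fixing it at 1 has two costs:

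- **Precision.** The treatment difference has a larger standard error than the same data could give.
- **Conditional bias.** If one arm happens to start with worse scores at M3, regression to the mean makes it appear to improve more. Subtracting M3 over-corrects for the starting difference.

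Both costs matter more in a trial of 42 patients whose planned power has almost no margin and which makes no allowance for drop-outs. The unadjusted analysis is a choice stated in the protocol. It has not been left open for an analysis plan to settle.

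**Working it through.** **Inputs from the protocol.** Difference 8, SD of change 9, 21 per arm, two-sided 5%. **Assumptions.** Rho between M3 and M6 is not given, so a range is shown. Variances at M3 and M6 are taken as equal, and the SD of change is held at 9.

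**1. The plan's own figure.** The standard error of the difference in change is 9 × √(2/21) = 2.78. The noncentral t with 40 degrees of freedom gives 80.3% power at 21 per arm and 78.2% at 20. The stated 42 is therefore correct for the planned test.

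**2. Variance ratio.** With score SD σ, Var(change) = 2σ²(1 − rho), and the ANCOVA residual variance is σ²(1 − rho²). The ratio is (1 + rho)/2, so the effective SD is 9 × √((1 + rho)/2).

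**3. Small-sample penalty.** Estimating the slope costs one degree of freedom (39 remain) and inflates the variance by about 1 + 1/38. Power at 21 per arm, M3 as the only covariate:

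| rho | Variance ratio | Effective SD before penalty | Power after penalty |
|---|---|---|---|
| 0.3 | 0.65 | 7.26 | 93% |
| 0.5 | 0.75 | 7.79 | 89% |
| 0.7 | 0.85 | 8.30 | 85% |
| 0.8 | 0.90 | 8.54 | 83% |
| 0.9 | 0.95 | 8.77 | 81% |
| 0.95 | 0.975 | 8.89 | 80% |

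A simulation of 20,000 trials per setting gave 89.3% at rho 0.5 and 85.0% at rho 0.7 for ANCOVA, and 80.0% and 80.1% for the t-test.

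**4. Adding M0.** If all pairs of visits have the same correlation (compound symmetry), the ratio becomes (1 + 2·rho)/(2(1 + rho)): 0.667 at rho 0.5 and 0.722 at rho 0.8. Penalised power is then about 94%, 92%, 90%, 90% and 89% at rho 0.3, 0.5, 0.7, 0.8 and 0.9. If the correlation decays with time in a first-order autoregressive pattern, M0 adds nothing once M3 is in the model.

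**5. Chance imbalance.** Given an M3 difference of d points between arms, the change-score estimate shifts by −(1 − rho)·d. The score SD implied by a change SD of 9 is σ = 9/√(2(1 − rho)).

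- rho 0.5: σ = 9.0. The standard error of the M3 difference is 9.0 × √(2/21) = 2.78, and a one-standard-error imbalance shifts the estimate by 0.5 × 2.78 = 1.4 points.
- rho 0.7: σ = 11.62. The standard error is 3.59, and the shift is 0.3 × 3.59 = 1.1 points.

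The simulated slopes of the estimate on the imbalance were −0.51 and −0.30 for the change score, and close to 0 for ANCOVA.

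**6. Which rho is plausible.** A change SD of 9 with rho 0.9 implies a score SD of 9/√0.2 = 20.1. Scores below 15 are excluded and the scale ends at 60. A uniform spread over 15–60 has SD 45/√12 = 13.0, which corresponds to rho = 1 − 81/(2 × 168.75) = 0.76. This is a plausibility check and not a bound, but it makes values near 0.9 unlikely if the planning SD is right.

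**The case against.** The strongest reply is that nothing here is an error. Endpoint, sample size and test agree with one another, and the t-test on change is unbiased over randomisations and controls type I error. The gain depends on a correlation the protocol does not state, and it is about one power point at rho 0.9. This reply stands, and it limits the point to efficiency and conditional bias.

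Four stronger readings are tempting, and the documents do not support them:

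- **That a chance M3 imbalance passes straight into the estimate.** That would be true of a comparison of raw M6 scores. The change score leaves a share of (1 − rho), with the sign reversed.
- **That ANCOVA is more precise whenever rho is below 1.** That is a large-sample statement under equal variances. With 42 patients, the cost of estimating the slope cancels the M3-only gain at about rho 0.95.
- **That the M0 score goes unused.** The protocol imputes missing M3 or M6 values by chained equations without listing the predictors, and M0 may be among them. What can be said is that no planned comparison names M0 as a covariate.
- **That adding M0 is sure to bring a large gain.** The gain in step 4 needs compound symmetry. The exclusion of scores below 15, if applied at entry, also truncates M0 and fits poorly with equal variances.

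It can also be objected that the change would come late, since the last patients were expected to finish in February 2018. However, no interim analysis is planned, and the change can be fixed without sight of outcome data by arm.

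**Conclusion.** The point holds as an efficiency recommendation. It is not a fault in the type I error rate or in the sample size. At 42 patients the planned test has 80.3% power. ANCOVA on M3 would have about 83–89% for rho between 0.8 and 0.5, 93% at 0.3 and 81% at 0.9, and practically no gain by 0.95. It would also remove the over-correction of about 1.4 points (rho 0.5) or 1.1 points (rho 0.7) per standard error of imbalance at M3. The direction is secure for any plausible rho. The size rests on an assumed rho, equal variances at M3 and M6, and the planning SD of 9. The gain is worth having because the planned power leaves no room for losses: with 19 per arm contributing data, the t-test falls to 76%, while ANCOVA on M3 keeps 86%, 81% and 79% at rho 0.5, 0.7 and 0.8.

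**What to change.** Before unblinding, replace the main primary analysis with an ANCOVA of the M6 MGQOL-15-F score on arm, M3 score and centre (the stratification factor), optionally with M0. Fit it within the multiple imputation already planned, and report the adjusted mean difference with its 95% confidence interval. Using the M3–M6 change as the response gives the identical arm coefficient once M3 is a covariate, so the stated outcome and the 8-point target do not change. Decide on M0 in advance.

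Use the same form for continuous secondary outcomes that have an M3 value: MMS, MG-ADL, FVC, MIP, MEP, limb strength, grip, six-minute walk distance, STAI, BDI-13 and WHOQOL-BREF. Keep the unadjusted t-test on change as a sensitivity analysis.

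The cost is one paragraph of text and 2 degrees of freedom (M3 and centre, leaving 38), or 3 with M0 (leaving 37), against 40 for the t-test. No new data are needed.

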**Fig 2 Fig2:**
[figure not shown]
Standard protocol items recommendations for interventional trials (SPIRIT). Schedule of enrolment, intervention and assessments. M0 includes enrolment and informed consent signing. Visits are monthly (M). Randomisation and allocation takes place following the 3-month visit (M3). Intervention period is 3–6 months. Post-intervention evaluation is at M6. *Evaluator blinded to treatment allocation

Safety evaluations are monthly; muscular and psychological evaluations are three-monthly (M0, M3, M6 and M9). The intervention period is between M3 and M6. The study has been approved by an ethics committee in accordance with French regulations (*Comité de Protection des Personnes Ile de France XI* under the CPP number #13064 on 13 December 2013 and authorised by the *Agence National de Sécurité du Médicament et des produits de santé* on 11 October 2013). The trial is conducted in accordance with the Helsinki Declaration [24]. Each participating patient receives written and verbal explanations about the study and evaluation procedures. The trial is registered in the ClinicalTrials.gov registry (NCT02066519). Reporting of the study will adhere to the Consolidated Standards of Reporting Trials (CONSORT) guidelines and the Standard Protocol Items: Recommendations for Interventional Trials (SPIRIT) [25–27]. The SPIRIT checklist is available as an Additional file 1.

Participating centres include the neuromuscular and neurological intensive care departments, Pitié-Salpêtrière Hospital, Paris, the Raymond Poincaré Hospital, Garches (Paris region) and Rothschild Hospital, Paris.

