### Recruitment and trial participants

All patients presenting for a regular out-patient consultation with their neurologist in one of two university hospitals in Île-de-France, France (Pitié-Salpêtrière, Paris and Raymond Poincaré, Garches), are screened for eligibility. Both hospitals are specialist centres for the management of MG. Eligible patients are invited to participate and a date is organised for study inclusion. Information about the study is also advertised by the French Association against Neuromuscular Disorders (AFM) myasthenia group and various social media patient groups. Information flyers are displayed in the two university hospital waiting rooms.

Adult patients with a diagnosis of mild or moderate generalised MG (II or III on the Myasthenia Gravis Foundation of America [MGFA] classification) are considered for eligibility [29]. Diagnosis should be confirmed by the presence of circulating antibodies against acetylcholine (AChR) or muscle-specific kinase (MuSK) or low density lipoprotein receptor-related protein 4 (LRP4) receptors or abnormal repetitive nerve stimulation testing (decrement > 10%) on EMG or abnormal single fibre EMG (conduction block or jitter) or based on their clinical history and symptom improvement with acetylcholinesterase inhibitors. The MG must be stabilised for at least six months before entry into the study; thus, duration of the disease must be at least six months but is otherwise unrestricted. Both men and women aged 18–70 years are eligible for inclusion. For practical reasons (due to multiple visits and rowing machine delivery), participants should live in Paris or in the surrounding Paris region; they agree to be able to participate in the exercise program and can house the rowing machine for the three-month duration in their home. They should be affiliated with the national social security system.

Exclusion/non-inclusion criteria:

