### Randomisation, allocation and blinding

Figure 1 depicts the participants’ flow through the study according to the CONSORT guidelines [25, 26]. Figure 2 presents the timeline of assessments and intervention. Following study inclusion, there is a three-month observation period to ensure disease stability (in addition to the six-month stability required before inclusion). All consecutive participants are then randomly assigned to either the control or experimental group with a 1:1 allocation ratio as per a computer-generated randomisation schema stratified by centre using permuted blocks of randomly varying sizes. To ensure concealment, the block sizes are not disclosed. Group allocation is revealed via a computer software (CleanWeb) exclusively to the non-blinded physiotherapist once randomisation has been performed (concealed allocation). The physiotherapist then informs the patient verbally. The randomisation list was constructed prior to the beginning of the study by an off-site independent statistician with no clinical involvement in the study.

Clinical and psychological evaluations are performed by blinded assessors. As randomisation takes place three months after inclusion, the physiotherapist is unaware of group allocation for the first two evaluations (M0 and M3). Patients are informed not to disclose their allocation to their treating neurologist or psychologist. Throughout the study all participants are requested to maintain their regular lifestyle, the only difference being the three-month exercise period for the experimental group which is lacking for the control group.

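### Randomisation is stratified by centre but the main analysis leaves centre out, which forgoes some precision if centres differ in mean change; the number of centre strata also needs clarifying

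*Protocol article*

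**What the plan says.** All references are to the protocol article.

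- **Randomisation, allocation and blinding:** allocation is 1:1 by a "computer-generated randomisation schema stratified by centre using permuted blocks of randomly varying sizes".
- **Statistical analysis:** "The main analysis of the primary and secondary outcome measures will not be adjusted". The next sentence reads: "Adjusted analyses on the centre will be performed but considered as secondary analyses".
- **Patient description and follow-up:** the change in MGQOL-15-F "will be analysed via a Student’s test and adjustment on the centre will use ANOVA".
- **Secondary outcome measure analysis:** continuous outcomes follow the same pattern (Student's test, then ANOVA with centre). Binary outcomes get Fisher's exact test, then logistic regression with centre.
- **Number of centres:** the Statistical analysis section says "As there are only two centres, the centre will be modelled as a fixed effect". Recruitment and trial participants also counts two, since patients seen "in one of two university hospitals in Île-de-France, France (Pitié-Salpêtrière, Paris and Raymond Poincaré, Garches), are screened for eligibility". Study design, ethics, consent and permission (the text after Fig. 2) lists three participating hospitals, the list ending "Garches (Paris region) and Rothschild Hospital, Paris". The article describes no role for the third and does not give the number of randomisation strata.

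**The concern.** Blocking within centre forces near-equal numbers of both arms in each hospital. Any difference between hospitals in mean change then largely drops out of the arm comparison. The plain two-sample t-test does not know this and still counts between-centre variation as error. Its reported standard error then exceeds the true one, the confidence interval is too wide, and the actual type I error is below 5%.

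The analysis that matches the randomisation is already planned, but in a secondary role. At stake is the precision of the headline estimate in a trial of 42 patients sized at almost exactly 80% power with no allowance for drop-outs. The choice is stated outright, so it is not a detail left to an unseen analysis plan.

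The centre term in the adjusted model must also equal the randomisation stratum, and the article leaves the number of strata open.

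**Working it through.** **Inputs from the Sample size calculation section:** difference 8, SD of change 9, 21 per arm, two-sided 5%, power 80%.

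**Assumptions (not in the protocol):** two strata; centre split 50:50 or 70:30; difference *d* between centres in mean change of 0 to 8 points; total SD held at 9.

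**Step 1: reproduce the planned sample size.** The normal approximation gives n = 2(1.96 + 0.84)² × 9²/8² ≈ 20 per arm. The noncentral t gives 78.2% power at 20 per arm and 80.3% at 21. The stated 42 is therefore right for the unadjusted t-test.

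**Step 2: standard errors.** Unadjusted: 9 × √(2/21) = 2.777. With *p* the share of patients in one centre, the within-centre SD is √(81 − p(1−p)d²), and the adjusted SE is that SD × √(2/21). For example, at 50:50 and d = 6 the SD is √(81 − 9) = 8.49, the adjusted SE is 2.619, and 2.777/2.619 = 1.061.

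| *d* (points) | Adjusted SE, 50:50 | Unadjusted SE too wide by, 50:50 | Same, 70:30 | Adjusted power, 50:50 / 70:30 |
|---|---|---|---|---|
| 0 | 2.777 | 0% | 0% | 80.2% / 80.2% |
| 2 | 2.760 | 0.6% | 0.5% | 80.7% / 80.6% |
| 4 | 2.708 | 2.6% | 2.1% | 82.1% / 81.8% |
| 6 | 2.619 | 6.1% | 5.0% | 84.6% / 83.9% |
| 8 | 2.488 | 11.6% | 9.5% | 88.0% / 86.8% |

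**Step 3: simulation check.** 10,000 trials per setting, 42 patients, two centres, blocks of 2, 4 and 6 within centre (block sizes assumed). Entries are unadjusted / adjusted.

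| *d* | Type I error, 50:50 | Power, 50:50 | Type I error, 70:30 | Power, 70:30 |
|---|---|---|---|---|
| 0 | 5.0 / 4.9% | 80.7 / 80.5% | 5.1 / 5.1% | 80.6 / 80.4% |
| 2 | 5.3 / 5.4% | 79.3 / 79.6% | 5.2 / 5.3% | 80.3 / 80.5% |
| 4 | 4.6 / 5.1% | 80.0 / 81.3% | 4.4 / 5.0% | 80.5 / 81.9% |
| 6 | 3.8 / 4.9% | 81.5 / 84.7% | 4.0 / 5.1% | 81.6 / 84.1% |
| 8 | 3.0 / 4.8% | 82.9 / 88.8% | 3.5 / 5.5% | 81.8 / 86.8% |

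The Monte Carlo standard error is √(0.05 × 0.95/10,000) ≈ 0.2 points for type I error and √(0.8 × 0.2/10,000) = 0.4 points for power. The 79.3% at d = 2 should be read as noise: the adjusted test on the same runs is also about one point below its calculated 80.7%. A separate simulation with a 28/14 split gave 80.7% unadjusted and 81.1% adjusted at d = 2.

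At 50:50 and d = 6, the estimate's true standard error is about 2.63 while the t-test reports about 2.77. Unadjusted power still rises slightly with *d*, because the estimate itself becomes less variable under blocking.

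**Step 4: what a variance share means in points.** d = 9 × √(R²/[p(1−p)]). For a 28/14 split, p(1−p) = 2/9. Centre explaining 10%, 20% or 30% of the variance of change therefore means differences of 6.0, 8.5 or 10.5 points.

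**The case against.** The strongest reply concerns size.

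- **Only differences in mean change matter.** The primary outcome is the change from month 3 to month 6, so a constant level difference between hospitals cancels.
- **Large centre effects are not obvious here.** The scale is self-administered, the programme is home-based, and the two recruiting hospitals are specialist centres in one region. A centre difference of 8 points in change would equal the whole target treatment effect.
- **Below about 4 points the effect is under 3% of the standard error**, and the centre-adjusted result will be reported anyway.

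All of this stands, and it limits the size of the point. It does not remove it: the adjusted analysis performs practically the same when centres do not differ and better when they do.

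A reader might infer that the main test is invalid, biased or short of the planned power. The protocol does not support that. The unadjusted estimate is unbiased, its type I error does not exceed 5% beyond simulation noise, and its power does not fall below the planned 80%.

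A reader might also extend the argument to the binary outcomes. That does not follow. There, promoting the adjusted analysis would replace an exact test with logistic regression in 42 patients and change the odds ratio being estimated.

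Finally, the three-versus-two count might be read as a proven contradiction. The third hospital is listed as participating, and it could do so without recruiting or randomising. The article does not say, so this is an ambiguity.

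**Conclusion.** The point holds as a mismatch between design and main analysis with a modest cost. For continuous outcomes, the unadjusted standard error is too wide if centres differ in mean change:

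- by about 0.5–3% for differences of 2–4 points;
- by 5–6% at 6 points, with type I error about 3.8% and power about 81% against 84–85% adjusted;
- by about 10–12% at 8 points, with type I error about 3% and power about 83% against 88%; the 50:50 split gives the larger figures.

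The error is zero if centres do not differ. These sizes rest on assumed centre differences, splits and block sizes, with 42 patients and a total SD of 9. What is lost is precision that the stratified design could have delivered. The change is worth making because it is nearly free.

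The number of centre strata cannot be determined from the article and needs one clarifying statement.

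**What to change.** 1. In the Statistical analysis and Patient description and follow-up sections, make the centre-adjusted ANOVA the main analysis of the change in MGQOL-15-F, and keep the unadjusted Student's test as a sensitivity analysis.
2. Do the same for the continuous secondary outcomes. Leave the binary outcomes as planned.
3. Define centre as the stratum used in the randomisation list.
4. State whether the third hospital randomises patients, and make the Study design, Recruitment and trial participants, and Statistical analysis sections agree on the number of centres.

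Cost: a swap of labels between two analyses already planned, and one degree of freedom (two if there are three strata). No extra patients or data are needed. If centres turn out not to differ, calculated power is 80.2% instead of 80.3%.
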